### Outcome measures

The primary outcome is the composite of de novo DSA (defined as mean fluorescence intensity [MFI] of over 500), or any biopsy-proven acute rejection or allograft loss (defined as returning to dialysis or death with functioning allograft) after parental donor kidney transplantation up to 60-months post-transplant. Secondary outcomes are individual components of the primary composite outcome (development of de novo DSA, any biopsy-proven acute rejection, allograft loss at 60-months post-transplant but also extended follow-up to 120-months post-transplant), acute or chronic AMR (including the presence of TG) or Chronic Allograft Damage Index (CADI) score of > 1 on allograft biopsy post-transplant, allograft function (creatinine-derived estimated glomerular filtration rate [eGFR] using the Chronic Kidney Disease-Epidemiology Collaboration [CKD-EPI] equation for recipients aged ≥16 years [32] or bedside Schwartz equation for recipients aged < 16 years [33–35]), and urine proteinuria.

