### Statistical analysis

Data will be presented as mean ± standard deviation (SD) or number (proportion) for continuous and categorical variables, respectively, with means and proportion compared using *t-test* and the chi-squared test where appropriate. We will develop models with different numbers of archetypes and choose which to use as the final model according to the residual sum of squares using the “elbow” method [47]. The archetypal models will assign scores based on a combination of pre-transplant immunological and clinical (donor, recipient and transplant) parameters to each recipient using the time from transplant to the composite primary outcomes of de novo DSA, any episodes of acute rejection and allograft loss; with the scores totalling 1. Each parameter will be assigned to a single archetype cluster on the basis of the highest archetype score (corresponding to “high immunogenic risk” profile, comprising of immunological risk factors). Additional models accounting for pre- and post-transplant factors (such as donor age, non-adherence) will also be constructed. A principal component analysis will be constructed to visualize the data matrix used as the input for the archetypal analysis. The principal component analyses will produce two main results: (i) a correlation circle, and (ii) a projection of the individuals. The correlation circle allows for a graphical examination of the relationships among the pre-transplant immunological and clinical parameters and the graphical parameter contribution of the axes (positive or negative contribution: vector direction; strength of the contribution: vector length when projected on the axis). We will identify distinct groups (i.e. archetypes), each comprising of a well-defined set of immunological and clinical parameters that may improve the risk stratification for “adverse immunological outcomes” for those accepting a parental donor kidney for transplantation, and separately for those who have received maternal or paternal donor kidneys. The Australian and New Zealand cohorts will be the derivation cohort for these archetypes, which will be validated in the cohorts from the United Kingdom and the Netherlands. We will next seek to build a predictive model (combined cohorts) to examine the associations between the archetype clusters and other pre-specified covariates and the primary outcome using univariate Cox proportional hazards regression models. A multivariable Cox model will be constructed by selecting covariates by Group Lasso and Doubly Robust Estimation (GLiDeR), a method of variable selection to identify confounders using an adaptive group lasso approach that simultaneously performs coefficient selection, regularisation, and estimation across the treatment and outcome models. Bootstrap resampling with replacement or subsampling without replacement will be used to investigate and quantify model stability. Separate models will be constructed for each of the secondary outcomes. The results of the model and covariates will be reviewed to ensure clinical relevance. Deviance and score residuals will be plotted to evaluate for poorly predicted individuals or individuals that may have had large influences on model parameters. The performance of the integrated prognostic model will be assessed by computing a non–time-specific area under the curve (AUC) using the measure of concordance from Somer’s Dxy statistic. For assessment of model calibration, patients will be risk-stratified on the basis of their predictive index, which is the linear combination of the product of the multivariate model β coefficients and their individual covariate values. Kaplan-Meier survival curves will then be plotted for patients who are stratified into quintiles of their predictive indices. The validation cohort’s AUC will be determined and predicted and observed mortalities will be compared. The association between archetypes and adverse outcomes will be examined in the prospective cohort, and to examine how the addition of other newly developed novel immunological assays will improve the test performance of the models.

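### The AUC reported for the validation cohort probably comes from patients used to fit the Cox model, and predicted risk is checked against mortality, not the modelled composite

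*Protocol article*

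**What the plan says.** All steps are in the Statistical analysis section of the protocol article, in this order.

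- Archetypes: "The Australian and New Zealand cohorts will be the derivation cohort for these archetypes". The test set for them is then named: "which will be validated in the cohorts from the United Kingdom and the Netherlands". No other validation cohort is defined in the article.
- Predictive model: "We will next seek to build a predictive model (combined cohorts) to examine the associations between the archetype clusters", other covariates and the primary outcome, starting with univariate Cox models. A multivariable Cox model follows, with covariates chosen by GLiDeR, an adaptive group lasso method.
- Resampling: "Bootstrap resampling with replacement or subsampling without replacement will be used to investigate and quantify model stability".
- Calibration: patients are grouped by predictive index, and "Kaplan-Meier survival curves will then be plotted for patients who are stratified into quintiles of their predictive indices".
- Validation: for the validation cohort, "AUC will be determined and predicted and observed mortalities will be compared".

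The outcome being modelled is set under Outcome measures: "The primary outcome is the composite of de novo DSA", biopsy-proven acute rejection or allograft loss up to 60 months. Death enters only as death with a functioning allograft, inside allograft loss.

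**The concern.** Two things do not fit together.

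1. **Overlap.** If the Cox model is selected and fitted on all four countries, UK/Netherlands is development data. Scoring the model there and reporting the result for a validation cohort presents apparent performance as external performance.
2. **Event.** Comparing predicted with observed mortality does not test a model of the composite. Predicted composite risk and observed deaths are different quantities, so the comparison cannot show whether the predictions are right.

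The Discussion says the study will validate the predictive power of the mismatch scores and improve the choice of parental donor. Readers would take the validation AUC and the predicted-versus-observed comparison as the evidence for that. The association aims and the maternal-paternal comparison are not biased by this problem.

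**Working it through.** The article gives no performance figure to reproduce, so the check sets the steps side by side and then sizes the consequence.

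**Step 1: who is in which set**

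| Step | Patients used |
|---|---|
| Archetype derivation | Australia, New Zealand |
| Archetype validation | UK, Netherlands |
| Predictive Cox model | all cohorts combined |
| AUC of the validation cohort | UK, Netherlands (the only one defined) |

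The archetype step is properly split. The Cox step is not.

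**Step 2: how large the overlap is.** Inputs are the transplant counts that follow Fig. 2 in Sample size calculation. Yearly parental transplants:

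- Australia: 182 × 0.40 / 4 = 18.2
- New Zealand: 30 × 0.67 / 4 = 5.0
- Netherlands: 30 × (0.30 to 0.40) / 4 = 2.25 to 3.0
- UK: 340 / 6 = 56.7, or 340 / 5 = 68.0, depending on how 2010-2015 is counted

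UK/Netherlands share, assuming recruitment in proportion to these rates:

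- low: (56.7 + 2.25) / (56.7 + 2.25 + 18.2 + 5.0) = 0.72
- high: (68.0 + 3.0) / (68.0 + 3.0 + 18.2 + 5.0) = 0.75

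Of 520 pairs, about 373-392 would be UK/Netherlands and 128-147 Australia/New Zealand. Most of the fitting data would be the patients later used for validation.

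**Step 3: size of the optimism.** Assumptions, none stated in the article: 20-40 candidate predictors; adaptive-lasso Cox as a stand-in for GLiDeR; 520 pairs, of which 374 are UK/Netherlands; 40 replicates per setting. The penalty was tuned either by cross-validation (40% events; 20 and 40 candidates) or by BIC (35% events; 20 and 30 candidates; four true predictors with log hazard ratio 0.25 where there is a signal). Optimism is C in the overlapping cohort minus C in new patients.

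| Signal | Tuning | Candidates | C, overlap | C, new | Optimism |
|---|---|---|---|---|---|
| modest | CV | 20 | 0.645 | 0.622 | 0.023 |
| modest | CV | 40 | 0.659 | 0.615 | 0.044 |
| modest | BIC | 20 | 0.638 | 0.614 | 0.024 |
| modest | BIC | 30 | 0.633 | 0.608 | 0.025 |
| none | CV | 20 | 0.555 | 0.499 | 0.056 |
| none | CV | 40 | 0.583 | 0.501 | 0.082 |
| none | BIC | 20 | 0.507 | 0.50* | 0.007 |
| none | BIC | 30 | 0.511 | 0.50* | 0.011 |

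*Taken as 0.50, because there is no signal.

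This gives about 0.02-0.04 with a modest signal and 0.01-0.08 with none. A separate repeat with 20 and 40 candidates and both tunings gave differences inside both ranges.

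**Step 4: composite against mortality.** Sample size calculation assumes a composite rate of up to 40% by 60 months: 520 × 0.40 = 208 events overall, and 374 × 0.40 ≈ 150 in UK/Netherlands. The article gives no death rate. Assuming 1-5% by 60 months, deaths would be 520 × (0.01 to 0.05) ≈ 5-26 overall and 374 × (0.01 to 0.05) ≈ 4-19 in UK/Netherlands. Average predicted composite risk would exceed observed mortality by 0.40/0.05 = 8 to 0.40/0.01 = 40 times, even for a perfectly calibrated model.

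**The case against.** The strongest reply has three parts.

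- **The combined-cohorts remark sits in the sentence on associations and univariate models.** The multivariable sentence names no cohort, so that fit might be meant for Australia/New Zealand only. This stands as an ambiguity. But the sentence announces the predictive model as a whole, so the combined fit is the likelier reading, and on either reading the text does not say which patients the model is fitted on.
- **The plan penalises.** This stands and limits the size. An unpenalised Cox model with 20-30 predictors and no signal gives C of 0.59-0.61 in the overlapping cohort, and a reader might take that as the bias. The plan does not use that method, so that figure should not be attached to it.
- **Mortality may be a slip for events.** Possibly, but as written it fixes the wrong comparison.

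Other inferences go further than the article allows:

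- That the archetypes lack separate validation. They have it.
- That the AUC is for the wrong outcome. The Cox model is for the primary outcome, and nothing ties the AUC to mortality.
- That approaching only living pairs empties the mortality comparison. That restriction is stated for Australia/New Zealand, not for UK/Netherlands.
- That missing optimism correction, predicted curves on the Kaplan-Meier plots or a calibration slope are faults in themselves. A condensed article may leave these to the full plan.
- That the prospective cohort mentioned at the end either rescues or worsens the validation. It is assigned to archetype associations only.

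**Conclusion.** The point holds for the Cox model, on the likelier reading of the text: the cohort that supplies the validation AUC is also development data, and probably about 72-75% of it if recruitment follows the stated rates. The AUC would be biased upward. Under the assumptions in the working, the bias is about 0.02-0.04 in C with a modest signal and 0.01-0.08 without one. The direction is clear; the size depends on the candidate count and tuning and is illustrative. Separately, the one stated predicted-versus-observed comparison names mortality, which is only one part of one component of the outcome modelled. Both should be fixed before the model is described as validated. Neither affects the maternal-paternal comparison or the archetype validation.

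**What to change.** State which patients the multivariable Cox model is selected and fitted on, and choose one of two routes.

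- **(a) Hold out.** Select and fit without UK/Netherlands, freeze the model, and report C in UK/Netherlands; or run internal-external validation by country block. A fit in Australia/New Zealand alone would rest on about 128-147 pairs, or 51-59 events at 40%, which is about 1.3 (51/40) to 2.9 (59/20) events per candidate with 20-40 candidates. It will be imprecise.
- **(b) Keep the combined fit.** Report a bootstrap optimism-corrected C with covariate selection repeated in every resample, and call the model internally validated only.

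Under either route, replace the comparison of predicted and observed mortality with predicted versus observed 60-month risk of the primary composite.

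The cost is a wording change, more computing and a lower reported AUC. No additional patients or data are needed.

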
## Discussion

The INCEPTION study including parental donor kidney transplant recipients across 4 countries reflects a study cohort of diverse ethnic distributions, which will allow for the generalizability of findings. The presence of local site study investigators and the implementation of site-specific study processes and procedures will ensure that we achieve the target recruitment. The investigators/authors (and delegates) of the protocol manuscript and appointed consumer and registry representative(s) of each country will form the steering and data monitoring committee, which will convene bi-annually and address issues relating to the conduct of the research and adherence to study protocol and processes. Any change in protocol or data capture will need to be approved by the steering and data monitoring committee prior to implementation.

### Storage of genetic materials and serum for related future research projects

With the current funding restrictions for this study, not all HLA and non-HLA genes or identification of anti-HLA and non-HLA antibodies will be possible. Genetic materials and sera obtained from patients (and corresponding donors) will be stored for a period of 15 years after completion of the initial study until future funding for additional projects become available. The steering and data monitoring committee of this study will provide oversight of potential research proposals regarding the use of these specimens and de-identified health information for future related projects.

### Confidentiality, data storage and record retention

All data will be managed in a confidential manner. Data will be stored on a secure server and only authorized investigators in the study team or their delegates will have access to the data. Health-related data will be retained for at least 15 years after completion of the project and relevant publications. The additional DNA and sera that are extracted/isolated and stored will be kept in a local or central facility, which will be pre-identified prior to commencement of study. If participants withdraw consent during the research project, the study doctor and relevant study staff will not collect additional information, although personal and other relevant information already collected will be retained to ensure that the results of the research project can be measured properly and to comply with law. Genetic materials and sera obtained for the purpose of this study will be kept locally or centrally for 15 years following completion of the initial study, after which the specimens will be destroyed and discarded appropriately.

### Dissemination of outcomes of project

It is anticipated that the results of this research project will be published and/or presented in a variety of forums, including national and international medical conferences. In any publications and/or presentations, only aggregate information will be provided in such a way that no participants can be identified. The results of these findings will also be disseminated through a newsletter summarising the salient findings to all study investigators, site investigators and other relevant people directly involved in the care of kidney transplant recipients. A summary of the study findings in lay person’s language will be disseminated to the participants.

The INCEPTION study findings will provide evidence to support or refute the apparent contradictory paradigm of differential outcomes associated with maternal versus paternal transplants, which can inform healthcare providers, clinicians, patients and their families of potential risks and expected long-term allograft outcome after accepting maternal compared to paternal donor kidneys. As children and adolescents have a higher need for maximizing transplant survival, the INCEPTION study is critical to supporting the evidence base to improve survival particularly for children and adolescents with kidney failure. In addition, kidney transplantation is associated with improved cognitive functioning [48, 49], health related quality of life [50], educational attainment and life participation [51]. Hence maximizing first allograft survival has ensuing benefits through increased social integration and labour productivity at the societal level. The INCEPTION study is important to improve the understanding of the immunological differences between accepting a kidney from the mother or father, which has not been possible until the recent development and availability of cutting-edge technology. This proposed program of work will enable an improved selection of the best available parental donor kidneys for children and adolescents with kidney failure, with subsequent improvements in the health outcomes for this at-risk population. There is considerable uncertainty regarding the utility, clinical application and significance of some of these methods and this study will systematically evaluate and validate the predictive power of combining the existing and novel pre-transplant B- and T cell molecular mismatch approaches to establish the influence of genetic compatibility in determining adverse allograft outcomes.

Additionally, this resource will further stimulate research interest in this and related areas leading to further improvements in kidney transplant and patient outcomes for this and other populations. Specifically, these include:The predictive value of novel assessment of donor/recipient gene compatibility for adverse allograft and patient outcomes such as acute rejection, allograft loss, recurrence of primary kidney disease and other complications occurring after kidney transplantation.The potential for individualizing immunological risk assessment to reduce adverse allograft outcomes in kidney transplant recipients.Establishment of an important resource that will comprise the largest cohort of pediatric and adolescent kidney transplant recipients worldwide, with the availability of high-resolution HLA typing (using the most advanced typing technique in NGS sequencing) and complete allograft and patient data. The improvement of outcome in this cohort of patients is critical because of their projected lifespan, burden of chronic disease and the likelihood that these recipients will require repeat transplantation and continuing long-term utilization of healthcare resources in the treatment of their disease burden.

## Data Availability

Data sharing not applicable to protocol paper. Future study data will be presented within the manuscript and additional supporting files (where appropriate), but the availability of these data (in public repositories) will be according to each country-specific governance processes.

## Abbreviations

AMR: Antibody mediated rejection
AUC: Area under the cruve
ANZDATA: Australia and New Zealand Dialysis and Transplant
ANZCTR: Australian New Zealand Clinical Trials Registry
CADI: Chronic Allograft Damage Index
CKD-EPI: Chronic Kidney Disease-Epidemiology Collaboration
DSA: De novo donor-specific anti-HLA antibody
DNA: Deoxyribonucleic acid
EMS-3D: Electrostatic mismatch score
eGFR: Estimated glomerular filtration rate
GLiDeR: Group Lasso and Doubly Robust Estimation
HLA: Human leukocyte antigen
Ig: Immunoglobulin
MFI: Mean fluorescence intensity
NHMRC: National Health and Medical Research Council
NGS: Next generation sequencing
NIMA: Non-inherited maternal antigen
NIPA: Non-inherited paternal antigen
PRA: Panel reactive antibody
PAS: Periodic acid–Schiff
PIRCHE: Predicted indirectly recognizable HLA epitopes
SES: Socioeconomic status
STROBE: Strengthening the Reporting of Observational studies in Epidemiology
TG: Transplant glomerulopathy
UK: United Kingdom
